## 2. Materials and Methods

### 2.1. Study Design and Participants

The current study will have a quasi-experimental design with a control group, which will be target children enrolled in third grade of primary education from 26 schools of the province of Cádiz. The inclusion criteria that will be used will be: children belonging to the selected school, who are in the third grade of primary school, regardless of their age, who have the informed consent signed by their parents or legal guardians, who respond to the questionnaires and who undergo to the anthropometric measurements. The exclusion criteria will be that these requirements are not met.

The total number of study participants will be between 850 and 900 children. The parents of each schoolchild will be part of that same subject (father, mother and child are the same subject of study). The sample will be divided into two groups, the intervention group and the control group. The intervention group will contain around 450 schoolchildren and will be made up of 13 of the 26 school centers which will participate in the study. In this group, pre-intervention measurements will be performed, which will be explained later. A multimodal intervention will be developed, which will also be explained in detail later. Finally, post-intervention measurements will be made, which will be the same as the pre-intervention measurements. The control group will also contain around 450 schoolchildren and will be made up of the others 13 school centers which will participate in the study. It will be made up of the same number of schoolchildren. The difference with respect to the intervention group will be that the control group will not receive any educational intervention. Only the pre- and post-intervention measurements will be taken, to later compare the results with the intervention group and find out if an effect has emerged or not.

The province of Cádiz will be divided into four areas: Campo de Gibraltar (six schools), Jerez-Costa Noroeste (five schools), Sierra de Cádiz (nine schools) and Bahía de Cádiz-La Janda (six schools) (Figure 1). In each area, there will be between 200 and 300 participants and school centers belonging to both the intervention group and the control group. This division will be made to have a sample that is as representative as possible of the entire province of Cádiz.

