Both the selection of schools participating in the study and the assignment of them to the experimental group or control group will be made randomly from the list of public schools of the Cádiz Education Delegation. These randomizations will be carried out taking into account the schools belonging to each of the geographical areas in which the province of Cádiz will be divided, the socioeconomic condition of the population served, which will be determined from the Material Deprivation Index (MDI) of the section of the census in which the school is located [37], and the number of classes or corresponding lines of each center belonging to that age group. Randomization will be carried out in groups by schools, not individually. 

The group of schoolchildren will constitute the first level of analysis, and the schools will be the second level. This target population (children 8–9 years) has been selected due to the need to detect and solve the problem of childhood obesity in early stages to promote healthier lifestyle habits, and thus achieve health benefits that allow correct weight management from childhood until adulthood, and because, at this age, children are very receptive to receiving information that implies changes in habits [23].

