### 2.2. Calculation of the Sample Size

To determine the effectiveness of the intervention on the prevalence of overweight and obesity, the sample size necessary to test hypotheses has been calculated, comparing two proportions. We will compare the percentage of overweight and obesity of schoolchildren before and after the intervention in both groups (intervention and control) (paired data) and inter-group (independent data). In our case, for an estimated difference of proportions of 9% (35% vs. 26%) with a confidence level of 95% and a power of 80%, the minimum sample size required is 410 subjects in each group (intervention and control), which makes a total of 820 subjects. For the calculation of the sample, after reviewing the results obtained by different studies carried out in our environment, it has been assumed an estimated prevalence of overweight and obesity of a 35%, which was found by Villagrán et al. (2013) [9] in a population of Cádiz similar to that of this study.

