### 2.5. Statistical Analysis

A descriptive analysis of the main outcome variables will be carried out with measures of centrality, dispersion and 95% confidence intervals (CI), and percentages or prevalence for the categorical variables. Chi square tests will be used for categorical variables and *t*-test or ANOVA for continuous variables, which will be used for comparisons of percentages or means, respectively, when they have a normal distribution. The effectiveness will be studied by comparing the changes in the groups. Simple and multiple linear regressions and/or logistic regressions with the respective odds ratios (OR) and the 95% CI will be applied as an association measure. The grouping term will be modeled in the analysis to adjust the effect of the intraclass correlation and a multilevel test will be conducted. For this, several levels of grouping will be established. The first level will be constituted by the geographical areas of study, the second by the municipality, the third level of grouping will be the school center and the line or classroom, and the fourth and last will be given by the intervention (control and experimental group).

For the analysis of longitudinal data, MANOVA of maximum likelihood and least squares will be used under conditions of normality of the data (assuming that large sample sizes will be obtained). If the data are not normal, generalized linear models (GLM) will be used. As a strategy for the analysis of missing data, the analysis of missing values of the SPSS statistical package will be used. In most situations it is not possible to verify the association of the missing data with other variables that allow it to be used to impute them in a probabilistic way; the Little’s MCAR test will be used to determine if the missing data occurs completely randomly (“Missing Completely at Random Data: MCAR”) and if its imputation is necessary. If the value of p obtained is less than 0.5, it cannot be assumed that the data are completely lost by chance and a multiple imputation will be made.

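### Section 2.5 lists arm comparisons with and without a school level for a school-randomised study, and does not say which one decides effectiveness

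*Protocol article*

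**What the plan says.** Section 2.1 is clear about the unit of allocation: "Randomization will be carried out in groups by schools, not individually". The intervention group "will be made up of 13 of the 26 school centers which will participate in the study", and the other 13 schools are the control group. On size it says "The total number of study participants will be between 850 and 900 children". The same section makes children the first level of analysis and schools the second.

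Section 2.5 then sets out the analysis in this order:

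1. A descriptive analysis, followed by chi-square tests and t-test or ANOVA, "which will be used for comparisons of percentages or means, respectively".
2. A statement that effectiveness is judged from how the two groups change.
3. Linear and logistic regressions.
4. The clustering commitment: "The grouping term will be modeled in the analysis to adjust the effect of the intraclass correlation and a multilevel test will be conducted". Four grouping levels follow: geographical area, municipality, school with classroom, and finally the intervention (control or experimental).
5. In a new paragraph, for the longitudinal data, "MANOVA of maximum likelihood and least squares will be used under conditions of normality of the data", with generalized linear models if the data are not normal.

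Section 2.5 names four dependent variables: BMI, triceps skinfold, waist/hip ratio, and the prevalence of overweight and obesity. The document mentions the intraclass correlation but gives no value for it.

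**The concern.** Effectiveness is defined as a comparison of change between arms. That is a longitudinal question, so a reader would look to the longitudinal paragraph for the method. That paragraph names MANOVA or generalized linear models and says nothing of schools. The grouping term stands in the paragraph before it, after the regressions, and no sentence carries it across.

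The same arm effect could therefore be tested in three ways, and the results may disagree. A child-level test treats the roughly 34 children of a school as independent, although the arms differ by 13 schools against 13. If its p-value is below 0.05 and the multilevel p-value is not, the plan has no rule for choosing between them.

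The multilevel test is also not described in a form that could settle the matter. Arm is listed as a grouping level, whereas it is the effect to be estimated.

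**Working it through.** **Inputs**

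- Schools: 26, 13 per arm (section 2.1).
- Children: 850 to 900 (section 2.1), so the mean per school is m = 850/26 = 32.7 to 900/26 = 34.6.
- Nominal error: 5%, from the 95% confidence level in section 2.2. It is taken as two-sided because only that reproduces the stated sample size.
- ICC of the tested quantity: not in the document. Assumed 0.01 to 0.05, with lower and higher values shown.

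**Step 1: the plan's own figure.** For 35% against 26% with 80% power and pooled variance:

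n = [1.960 × √(2 × 0.305 × 0.695) + 0.842 × √(0.35 × 0.65 + 0.26 × 0.74)]² / 0.09² = 410 per group.

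This matches section 2.2 exactly; a one-sided test would give 323. The formula treats children as independent. It is used here only to fix the sidedness.

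**Step 2: design effect.** DE = 1 + (m − 1) × ICC. For example, with m = 34.6 and ICC 0.02, DE = 1 + 33.6 × 0.02 = 1.67.

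**Step 3: true error of a child-level test.** With no intervention effect, the test statistic has variance DE instead of 1, so the error is 2 × [1 − Φ(1.96/√DE)].

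| Assumed ICC | DE (m = 32.7 to 34.6) | True error of a nominal 5% test |
|---|---|---|
| 0.001 | 1.03 | 5.4% |
| 0.005 | 1.16 to 1.17 | 6.9% to 7.0% |
| 0.01 | 1.32 to 1.34 | 8.8% to 9.0% |
| 0.02 | 1.63 to 1.67 | 12.5% to 13.0% |
| 0.05 | 2.58 to 2.68 | 22.3% to 23.1% |
| 0.10 | 4.17 to 4.36 | 33.7% to 34.8% |

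**Step 4: simulation.** 20,000 trials were generated with 13 schools per arm, 34 children per school, and a true prevalence of 35% in both arms that varied between schools (beta-binomial). The unadjusted comparison of proportions rejected in 4.9% at ICC 0, 9.2% at 0.01, 13.0% at 0.02 and 22.5% at 0.05. A t-test on the 26 school proportions rejected in about 5% at every ICC.

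**Step 5: which of the named analyses is exposed.** Chi-square, t-test and ANOVA as named in section 2.5 have no school term. The MANOVA sentence states none. The multilevel test has a school level, and steps 2 and 3 do not apply to it if arm is tested against between-school variation. The inflation therefore depends on which result is taken as decisive, and section 2.5 leaves that open.

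**The case against.** The strongest reply is that the plan already commits to modelling the grouping and to a multilevel test, and that section 2.1 names children and schools as the two levels of analysis. On a natural reading, chi-square, t-test and ANOVA follow the descriptive sentence and are preliminary, and the clustered models come after. This largely stands. A reader might infer that the plan ignores clustering, or that the trial will have 9% to 23% false positives. The document supports neither: the inflation arises only if effectiveness is concluded from an analysis without a school term, and no sentence says it will be.

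It can also be said that a MANOVA may carry school as a nested factor, and that a maximum-likelihood MANOVA may loosely mean a mixed model. Both are possible. The text states neither, and a nested factor protects the arm test only if arm is tested against between-school variation.

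The ICC range is an assumption, and the ICC of change may differ from that of levels. Section 2.1 also says that allocation takes account of area, deprivation and number of classes, which the simulation does not reproduce. These points limit the figures, not the gap in the text.

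Finally, model detail is often left to an analysis plan. That is right for the exact small-sample method and for how descriptive intervals are computed, and neither is pressed here. It does not cover a protocol that names unsuitable tests beside a suitable one without ranking them.

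One more inference fails: that at ICC 0.02 every child-level p between 0.01 and 0.05 would lose significance once schools are respected. The design effect is an average. In simulation about 16% of such results stayed below 0.05 on the school-means test.

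**Conclusion.** The point holds as an unresolved choice between analyses. Section 2.5 does not tie the grouping term to the longitudinal analysis, does not name the deciding result, and misplaces the intervention as a grouping level.

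If the conclusion were drawn from the child-level tests, or from a MANOVA without a school term, the true error of a nominal 5% test would be about 9%, 13% or 23% at ICC 0.01, 0.02 or 0.05. It would be near nominal (5.4%) at 0.001 and about 6.9% at 0.005. These figures rest on 26 schools of about 34 children, equal school sizes, unstratified allocation and an assumed ICC for the quantity actually tested. With school as the unit of analysis the error stays at about 5%.

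**What to change.** In section 2.5, state for each of the four dependent variables that the arm effect on the pre-post change is decided by one school-adjusted model, linear or logistic as the variable requires. Arm enters as a fixed effect and is removed from the list of grouping levels; school enters as a random effect. The school effect must bear on the tested quantity, for example by modelling the change itself, or the post-intervention value with baseline as a covariate. Use a reference distribution suited to 26 schools, or analyse the 26 school means (26 − 2 = 24 degrees of freedom).

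Use this model in place of MANOVA for the arm comparison, and say that chi-square, t-test and ANOVA are descriptive only.

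The change is to wording and needs no new data. Its cost is wider intervals and less favourable p-values than child-level tests would give.

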### 2.3. “PREVIENE-CÁDIZ” [CADIZ-PREVENT] Intervention Protocol

The “PREVIENE-CÁDIZ” [CADIZ-PREVENT] intervention (S1) will have a multimodal nature and will be aimed at schoolchildren, their families and schools. The intervention activities/sessions will be implemented by the teachers at the school centers. The research team will train those teachers to implement the program, and parents in a face-to-face session, but not schoolchildren. To achieve this, before implementing the intervention, the management teams and teachers of the intervention group will receive training sessions managed by the CEP (Center for Teacher Education) of Cádiz from the research team. These sessions will last 10 classroom hours and will be aimed at updating knowledge on promoting healthy lifestyle habits (healthy eating, promoting physical activity, reducing sedentary lifestyle, the importance of sleep and promoting health based on resources). Moreover, the sessions will be addressed for the teaching context, and they will show how to use the tools available to implement the intervention. All the information covered will be made available to the teaching staff through the “Moodle” virtual tool that will allow the research team and teaching staff to be in permanent contact to resolve any possible doubts. There will also be chat tools for management teams and research teams.

The intervention will be implemented in three settings: classroom, family and school. See the description of each setting below.

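### Little's MCAR test, at a printed threshold of p < 0.5, decides whether missing data are imputed; one method should be fixed in advance, and the data-completion eligibility criteria need a time point

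*Protocol article*

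**What the plan says.** On missing data, section 2.5 (Statistical Analysis) first remarks that the link between missingness and other variables can seldom be verified. It then uses Little's test to establish whether data are MCAR and "if its imputation is necessary". The decision rule is "If the value of p obtained is less than 0.5, it cannot be assumed that the data are completely lost by chance", in which case "a multiple imputation will be made". No action is stated for p of 0.5 or more, and nothing elsewhere in the article corrects the threshold. The same section also plans a multilevel analysis and, for longitudinal data, MANOVA by maximum likelihood and least squares.

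On eligibility, section 2.1 (Study Design and Participants) includes third-grade children of the selected schools who have signed consent, and "who respond to the questionnaires and who undergo to the anthropometric measurements". It adds: "The exclusion criteria will be that these requirements are not met". It does not say whether this refers to the visit before the intervention, the one after it, or both.

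**The concern.** A missing-data method is meant to protect the estimate when the children who drop out differ from those who stay. Here the outcome is weight status, so reluctance to be weighed a second time could plausibly be related to it. Under the stated rule, protection is applied only if a test on the same data rejects MCAR. Failure to reject is not evidence of MCAR. It may reflect low power, and the test cannot see missingness that depends on the unobserved value itself.

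The eligibility wording matters because it could decide the analysis set before any imputation takes place. If a child must have completed both visits to be eligible, the children for whom imputation is intended are no longer in the study.

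**Working it through.** **Inputs.** Section 2.5: imputation if p < 0.5. Section 2.2: 35% vs 26%, 95% confidence, 80% power, 410 per group, 820 in total. Section 2.1: 850 to 900 children planned. The article gives no dropout rate.

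**1. The plan's own figure.** With pooled variance, a two-sided test and no continuity correction:

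n = [1.960 × √(2 × 0.305 × 0.695) + 0.842 × √(0.35 × 0.65 + 0.26 × 0.74)]² / 0.09² = 409.6, rounded up to 410 per group.

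This reproduces the stated figure, which is not in dispute. It serves only step 5.

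**2. What the printed threshold does under MCAR.** A valid p-value is uniform under the null hypothesis, so P(p < c) = c.

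- c = 0.5: imputation triggered in 50% of trials with truly MCAR data.
- c = 0.05: triggered in 5%.

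A simulation of Little's test agrees: 48.1% and 5.2%. It used 1,000 runs, 820 subjects, three correlated normal variables and 10% MCAR missingness in two of them.

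**3. Which branch can do harm.**

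| Truth | Test below threshold: impute | Test at or above threshold: imputation deemed unnecessary |
|---|---|---|
| MCAR | Unbiased if the imputation model is sound | Unbiased |
| Not MCAR | Suitable if missing at random | Biased if only complete cases are analysed |

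Only the lower right cell is a problem. Moving the threshold from 0.5 to 0.05 puts more trials into the right-hand column, so more non-MCAR trials land in that cell. Correcting the misprint alone would therefore not cure the rule.

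**4. The eligibility criterion beside the schedule.** Sections 2.4.2 and 2.4.3 and Table 3 place the main questionnaires and the anthropometry both before and after the intervention. Section 2.4.9 and Table 3 place the questionnaire on breastfeeding, delivery and birth weight (S7) after it only. Two readings follow.

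- *Entry only.* A child must complete the baseline assessments. This is compatible with imputing later losses. But "Randomization will be carried out in groups by schools, not individually", and before implementation "the management teams and teachers of the intervention group will receive training sessions". Section 2.6 puts the training workshops in Phase I (first year) and both evaluations in Phase II (second year). Even baseline completion therefore appears to follow school allocation, so selection could differ by arm.
- *Both visits.* A child without post-intervention data is ineligible. Only item-level gaps would be left to impute, which conflicts with section 2.5.

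The two readings give different analysis sets, and the text does not choose between them.

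**5. Room for loss.** 1 − 820/850 = 3.5%; 1 − 820/900 = 8.9%. Under the second reading, any greater loss takes the sample below the plan's own minimum. This concerns numbers only, ignores clustering, and says nothing about bias.

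**The case against.** Several points on the other side are sound.

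- *The 50% rate is not itself a harm.* Under MCAR both branches are unbiased. When data are not MCAR, 0.5 leads to imputation more often than 0.05 would. A reader might infer from the printed figure that the estimate is biased half the time; the plan does not support that. This objection stands, and the point is therefore about the gate and not the number.
- *Inclusion criteria normally govern entry.* Section 2.1 does not mention the post-intervention visit, and planning imputation fits an entry-only reading. A reader might infer that children lost after allocation become ineligible and that the plan contradicts itself. That is only one reading of an ambiguous sentence. What stands is that the time point is missing.
- *The article does not say that complete cases are used when the test is not significant.* It also names maximum-likelihood and multilevel methods, which can use incomplete records. This stands in part: a likelihood analysis of all available data would soften the problem, but least-squares MANOVA would not, and the article leaves open which applies.
- *Detail may be in an unseen analysis plan.* True of the imputation model. It does not excuse a decision rule that the article itself states.

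A reader might also want a figure for the bias, but any figure depends on what is assumed. Suppose 15% of overweight and 5% of other children are lost. In a 35% arm the observed prevalence becomes 0.35 × 0.85 / (0.35 × 0.85 + 0.65 × 0.95) = 32.5%, a shift of 2.5 points if only that arm is affected. With the same loss in the other arm, 26% becomes 0.221/0.924 = 23.9%. The difference is then 8.6 points instead of 9, a bias of about 0.4 points. Nothing in the article supports one pattern over the other. If such loss tracked baseline weight status, the test would probably fall below 0.5 and imputation would follow.

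**Conclusion.** The point holds in limited form. The stated rule is wrong in principle at any threshold, because non-rejection of MCAR is used as a reason not to impute and the method for missing outcomes is then chosen by the data. The printed 0.5 is probably a misprint and needs correcting or removing, but it errs towards imputing. Its 50% trigger rate under MCAR, which follows from the uniform distribution of a valid p-value, is arbitrary and not a source of material bias.

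The eligibility criterion is ambiguous in time. The conflict with the imputation plan arises only if it covers the post-intervention visit. The inference that baseline completion follows allocation rests on the phase dates for training and evaluation.

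The size of any bias cannot be derived from the document. The defect is worth correcting because it bears on who is analysed and how, and the correction is cheap.

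**What to change.** In section 2.5, delete the rule that makes imputation depend on Little's test; the test may still be reported descriptively. Name in advance one primary method valid under MAR: either the multilevel model already planned, fitted by likelihood to all available data, or multiple imputation that respects school clustering and includes arm and baseline outcome. Report complete cases as a sensitivity analysis.

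In section 2.1, define eligibility by third-grade enrolment in a selected school plus signed consent, and analyse every such child in the arm of the school. Completing questionnaires and measurements then becomes data collection and ceases to be a condition of eligibility.

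The cost is wording in sections 2.1 and 2.5 and modest extra analysis. Data collection does not change.

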#### 2.4.8. Health Resources

Health resources will be evaluated using the Photovoice qualitative technique [46]. This technique will consist of taking two photographs, one of a resource that encourages healthy eating and the other from a resource that encourages healthy physical activity. Once each family identifies two health resources, the students will return to work on it in the classroom, which means that this activity will involves two sessions in the classroom and at least one with the family. This technique will be used for a dual purpose: (1) to identify the main health resources/assets related to physical activity and diet available to families in the environment of each school; (2) for educational purposes, as this technique will be part of the activities of the intervention, with which it is intended that both schoolchildren and family members identify, become aware of and promote the use of previously identified resources/assets.

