#### 2.4.9. Breastfeeding, Childbirth Type and Birth Weight

The characteristics of breast milk intake, type of delivery and birth weight will be recorded after the intervention using a questionnaire for parents (S7), which has been created by the research team based on the information from the scientific literature determined as important about these variables related to childhood obesity [47,48,49,50,51].

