The dependent variables of our study will be BMI, skinfold thickness of the triceps, waist/hip ratio (as anthropometric variables) and the prevalence of overweight and obesity. As surrogate or intermediate variables we will analyze behaviors related to eating, physical activity and sedentary lifestyle, hours of sleep, knowledge and beliefs about eating and physical activity, as well as the physical condition (IFIS) [44,45] of the children.

In the models, possible covariates related to personal, family, school and environment characteristics will be analyzed. Especially will be analyzed: sex, birth weight, breastfeeding, sociodemographic characteristics, family socioeconomic level, level of physical activity and time of sedentary activities of the parents; behavior, knowledge and beliefs about family food and physical activity, participation of the school in the intervention and level of adherence, participation of the center in other health promotion programs, availability or use of the school canteen and the existence of health assets in the environment.

To determine the efficacy of the different components of the intervention, predictive models will be obtained for each of the outcome variables by backward multiple linear regression, in which all possible components are included and are progressively eliminated from lowest to highest contribution. To analyze the specific contribution of a certain component on a dependent variable, the semi-partial correlations will be obtained; this method allows the effect of the component to be controlled to be subtracted from the predictors being treated. The R^2^ values of the components measure their theoretical contribution and allow establishing a theoretical hierarchy among the components that will be used in the regression by blocks; by changing R^2^ the different contributions of the variables will be seen.

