Breastfeeding, delivery type and birth weight	Questionnaire addressed to family or legal guardians Name: CADIZ-PREVENT—Breastfeeding, childbirth and birth weight (S7) Number of items: 7 Reference: created by the research team based on the information from the scientific literature [47,48,49,50,51]	Post intervention measurements: within 2 months after the intervention
Participant satisfaction/reaction and adherence to the intervention	World Cafe Addressed to schoolchildren, family or legal guardians, teachers and management teams of four schools selected of the intervention group Reference: www.theworldcafe.com Questionnaire addressed to management teams of the intervention group Name: CADIZ-PREVENT Program Evaluation Questionnaire. Directors—Management teams (S8) Number of items: 14 Reference: designed by the research team of the CADIZ-PREVENT study Questionnaire addressed to teachers of the intervention group Name: CADIZ-PREVENT Program Evaluation Questionnaire. Teachers (S9) Number of items: 35 Reference: designed by the research team of the CADIZ-PREVENT study	Post intervention measurements: within 2 months after the intervention

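### The covariate list for the outcome models includes adherence, which exists only in the intervention arm after the intervention, and school participation, which repeats the arm

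*Protocol article*

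**What the plan says.** Section 2.5 (Statistical Analysis) studies effectiveness by comparing change between the groups. It uses linear or logistic regression and a multilevel model in which intervention versus control is already one of the terms. After naming the dependent and intermediate variables, it states that covariates will be analysed in the models and gives a list of those of special interest. The list includes "participation of the school in the intervention and level of adherence" and "availability or use of the school canteen and the existence of health assets in the environment". It also includes the parents' physical activity and sedentary time, and the family's behaviour, knowledge and beliefs about food and activity. The efficacy of the intervention's components is a separate, later paragraph, so the list is not confined to that analysis.

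Other sections show where these variables come from:

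- **Adherence.** Table 3 gives three sources, all after the intervention: questionnaire S8 to management teams of the intervention group, questionnaire S9 to teachers of the intervention group, and the "World Cafe Addressed to schoolchildren, family or legal guardians, teachers and management teams of four schools selected of the intervention group". Section 2.4.10 treats the adherence of children and caregivers partly as whether habits at home really changed.
- **Health assets.** Section 2.4.8 evaluates them by Photovoice and says that "this technique will be part of the activities of the intervention". Table 3 times it during the six intervention months.
- **Family variables.** The family questionnaire S4 is given before and after the intervention. The main hypothesis in the Introduction is that the intervention changes the habits of parents as well as children.

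**The concern.** A covariate in a between-arm model should be defined in both arms and should not be a consequence of the intervention. Adherence fails on both counts. A control school has no programme to adhere to, and an intervention school's value is known only once the programme has run. Part of its definition is also close to the result that the trial is meant to estimate.

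The adjusted intervention effect is at stake. If the list is followed as written, a null or very imprecise estimate could come from the adjustment alone, and readers could not tell that apart from an ineffective programme.

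**Working it through.** **1. The plan's own figure.** Section 2.2 states that "the minimum sample size required is 410 subjects in each group (intervention and control), which makes a total of 820 subjects", for 35% versus 26%, 95% confidence and 80% power. The pooled two-proportion formula is n = [z(0.975)·√(2·p̄·q̄) + z(0.80)·√(p1·q1 + p2·q2)]² / (p1 − p2)².

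- p̄ = 0.305, so √(2 × 0.305 × 0.695) = 0.6511.
- √(0.35 × 0.65 + 0.26 × 0.74) = 0.6480.
- n = (1.960 × 0.6511 + 0.8416 × 0.6480)² / 0.09² = 409.6, so 410 per group.

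The figure is reproduced. The point below does not depend on it, and the fix does not change it.

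**2. Participation.** Allocation is by school and controls receive no intervention (sections 2.1 and 2.5), so a participation indicator equals the arm indicator. A design matrix with an intercept, arm and participation has rank 2 for 3 columns, and the two effects cannot be separated. If participation is the treatment term, nothing is lost.

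**3. Adherence: what the software would do.**

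- *Left missing in controls.* Complete-case fitting drops the control arm, about 450 of some 900 children, and no between-arm contrast remains.
- *Imputed in controls.* The multiple imputation of section 2.5 would assign adherence to a programme that these schools never received.
- *Set to zero in controls.* Write the model as outcome = a + b·arm + c·adherence. Because adherence is 0 in every control, b is the predicted difference for an intervention school with zero adherence. It is an extrapolation away from the data and not the effect of the programme as delivered, which is b + c × (mean adherence).

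**4. Size of the zero-filled case (illustration).** These values are assumptions, since the documents give none: adherence mean 0.8 and SD 0.15 across intervention schools; 26 schools of 32 children; school variance 0.02; true total effect −0.25 in child-level SD units; 2,000 simulated trials per scenario, fitted by least squares.

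The correlation of adherence with arm is 0.97. The variance inflation factor is 1/(1 − 0.972²) ≈ 18.

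| Scenario | Arm alone: coefficient (SE) | Arm + adherence: coefficient (SE) |
|---|---|---|
| Effect does not depend on adherence | −0.25 (0.090) | −0.24 (0.42) |
| Effect works wholly through adherence | −0.25 (0.088) | 0.01 (0.41) |

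The standard error rises by 0.421/0.090 = 4.7 in the first row. Over all scenarios run, the ratio is about 4.7 to 4.9. That is a little more than √18 = 4.3, because only 13 school values inform the adherence slope. In the first row the ratio of effect to standard error falls from 0.25/0.09 = 2.8 to 0.24/0.42 = 0.6.

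**5. Family variables, if post-intervention values were used (illustration).** Suppose the intervention shifts a family-behaviour score by 0.5 SD. If that score carries half of the effect, adding it moves the arm coefficient from −0.25 to −0.12. If it carries the whole effect, the coefficient moves to about 0. With baseline values this bias does not arise.

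**The case against.** The strongest reply is that the article speaks of possible covariates. On that reading it gives a list of candidates, with model-by-model selection and the choice of visit left to an analysis plan that is not shown. The basic between-group comparison of change exists whatever candidates are explored. Part of this stands. Inclusion is not fixed for each model, and the World Cafe is analysed qualitatively, so it is not certain that a numeric child-level adherence score would enter a regression. But the article does name adherence among the covariates of special interest in the models, outside the component analysis, and does not confine it to the intervention arm. That is something it states, not something it leaves out.

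A reader might infer more than the documents support:

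- *The arm is entered twice.* The text does not say so. Participation may simply be the treatment term.
- *Health assets are missing for all 13 control schools.* This is an inference from Photovoice being an intervention activity and from controls having only the pre and post measurements. The list does not name Photovoice as the only source, and Table 3 does not restrict Photovoice to the intervention group as it does the World Cafe, S8 and S9.
- *The family variables are mediators in the model.* Baseline S4 values exist, and the article does not say that post-intervention values will be used.
- *Birth weight and breastfeeding are faulty because S7 is given afterwards.* They are settled long before allocation and the intervention cannot change them. S7 also shares its window with the outcome measurements, so a child who misses that visit generally lacks the outcome too. There is no case here for moving S7.
- *A definite share of the planned 9-point difference would be lost, such as half.* The documents give no mediated share, so no such figure on the prevalence scale can be defended.

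**Conclusion.** The point holds for adherence and, unless it is the treatment term under another name, for school participation. That adherence is post-intervention and comes only from the intervention group follows from Table 3 and needs no assumption. Nor does the consequence in kind: a between-arm model containing it either loses the control children or turns the arm coefficient into an extrapolation to zero adherence. The figures in degree (correlation 0.97, standard error up about 4.7- to 4.9-fold, coefficient between unchanged and zero) rest on the assumed adherence distribution and effect.

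For health assets and for parental and family variables the point is conditional: on assets coming only from Photovoice, and on post-intervention values being used. Sex, socioeconomic characteristics, birth weight, breastfeeding and pre-intervention participation in other health programmes are sound covariates, so the defect concerns part of the list only.

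**What to change.** In section 2.5, for the between-arm effectiveness models:

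- Keep arm as the single treatment term and delete school participation as a separate covariate.
- Restrict covariates to pre-intervention values already collected (baseline S4 family variables, S10 participation in other programmes, sex, socioeconomic variables) and to characteristics fixed before allocation, such as birth weight and breastfeeding.
- Remove adherence and any assets derived from Photovoice.
- Analyse adherence separately, within the intervention arm.

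This is a change of wording. It needs no new data, no change to the visit schedule and no change to the 410 per group. The only loss is that adherence is no longer examined in the between-arm model.
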